PD is associated with dysfunction of the frontal-striatal pathways, which compromises frontal cortical regions, including the dorsolateral prefrontal cortex (DLPFC). Neuroimaging studies report that higher executive function scores are associated with stronger connectivity related to the DLPFC among patients with PD [11]. Mild executive dysfunction in PD is also associated with abnormal suppression of the DLPFC at rest [11]. On the basis of this evidence, high-frequency stimulation to the DLPFC is a logical approach for a high-frequency rTMS protocol. Indeed, reviews of the literature indicate that high-frequency rTMS over the DLPFC for multiple sessions can improve cognitive function. A review by Jiang et al [9] concluded that high-frequency rTMS over the DLPFC for multiple sessions (compared to a single session) had a significant effect on executive function in patients with PD.

Initial rTMS studies that targeted the DLPFC and measured change in cognitive performance used a single-session protocol in patients with PD with intact cognitive function (PD-N). One session of high-frequency (25 Hz) rTMS to the right DLPFC among 10 patients with PD-N who were temporarily taken off their PD motor medications showed improvements in executive function (ie, strategic planning), measured using the Tower of London test [12]. The same research group found that 1 session of high-frequency (10 Hz) rTMS to the left DLPFC in another 10 participants with PD-N off their PD medications did not improve executive function, working memory, or psychomotor speed [13].

Two initial randomized double-blind placebo-controlled trials examined the effects of multisession rTMS targeted to the DLPFC on depression (primary outcome) and cognitive function (secondary outcome) among patients with PD-N. Both randomized controlled trials (RCTs) applied high-frequency (5 Hz [14] or 15 Hz [15]) rTMS to the left DLPFC over the course of 10 sessions. Both studies reported improved depression and cognitive function, particularly executive function as measured using the Stroop test [14,15] and Wisconsin card sorting test [15]. These cognitive improvements were maintained for 20 [15] to 30 [14] days after the last rTMS session.

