The NIH-EXAMINER establishes a 3-factor model defined by cognitive control, working memory, and fluency. A confirmatory factor analysis indicates that these 3 factors load on to 1 factor: the Executive Composite score [38]. The ecological validity of the composite score was assessed in 225 patients with various neurological conditions, including PD [45]. Exhibiting concurrent validity, the composite score is a robust predictor of real-world executive behavior, as measured using the Frontal Systems Behavior Scale [36]. Furthermore, poor composite scores correlate with atrophy in frontal cortical regions that mediate executive function [36]. In patients with PD, the sensitivity of the NIH-EXAMINER was compared to that of other commonly used tests of executive function recommended by the International Parkinson and Movement Disorder Society task force on PD-MCI [24]; the NIH-EXAMINER Executive Composite score was the most sensitive and specific in detecting cognitive impairment, with an effect size of 0.94 [36].

Secondary outcomes include change from baseline to end point in the cognitive control composite score from the NIH-EXAMINER, working memory composite score from the NIH-EXAMINER, delayed verbal memory score for the Hopkins Verbal Learning Test–Revised [30], total score on the oral version of the Symbol Digit Modalities Test [46], total score on the Hooper Visual Organization Test [33], total score on the Beck Depression Inventory–II [47], total score on the Beck Anxiety Inventory [48], total score on the Apathy Evaluation Scale [49], total score on the MoCA [50], total score on the PD Cognitive Functional Rating Scale [40], and total score on the Activity Measure for Post-Acute Care applied cognitive domain questionnaire [41].

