
Potential moderators of the effects of rTMS will be explored through Pearson correlations and regression analyses. Factors include, for example, age at study enrollment, age at PD onset, disease duration, MoCA score, levodopa equivalent dose, and change in mood (eg, depression, anxiety, and apathy). Blinding success will be reported alongside the primary results.

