### Strengths and Limitations

This is a rigorously designed RCT implementing strong blinding procedures. The placebo effect is a significant issue to consider in PD research in general and specifically in TMS [58,59] due to dopaminergic system involvement in expectation and reward processing. This may confound interpretation of TMS efficacy. To mitigate this, we use a double-blind, randomized sham-controlled design using a validated sham TMS coil that mimics the auditory and somatosensory experience of active stimulation without inducing cortical activity. Another strength of the study is that we apply gold-standard methods to define PD-MCI. Mood, such as depression and anxiety, can mediate test performance on cognitive assessments. Our study does not control for mood severity, which is a limitation of the study design; however, we will collect self-report mood assessments across time points. We will explore mood as a moderator of the cognitive effects of rTMS. Cautious interpretation of change in cognitive performance will have to be made in the context of mood.

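### The moderator analysis relies on Pearson correlations, names no factor-by-treatment interaction, and lists post-randomization change in mood as a moderator

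*Protocol article*

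**What the plan says.** The moderator plan is two sentences near the end of the section Data Management Methods: Statistical Methods in the protocol article. The first gives the method: "Potential moderators of the effects of rTMS will be explored through Pearson correlations and regression analyses". The second gives the candidates: "Factors include, for example, age at study enrollment, age at PD onset, disease duration, MoCA score, levodopa equivalent dose, and change in mood". The mood item is spelled out as "and change in mood (eg, depression, anxiety, and apathy".

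The only interaction named anywhere in the article is group-by-time. It appears in the adverse-event model and in the mixed models for the neuropsychological outcomes. No term crosses a candidate moderator with treatment.

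Mood comes up again in Strengths and Limitations. That section states: "Mood, such as depression and anxiety, can mediate test performance on cognitive assessments". Shortly afterwards it states: "We will explore mood as a moderator of the cognitive effects of rTMS". It also says that "we will collect self-report mood assessments across time points". Under Outcomes, the secondary outcomes measured as change from baseline to end point include "total score on the Beck Depression Inventory–II [47], total score on the Beck Anxiety Inventory [48], total score on the Apathy Evaluation Scale [49".

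**The concern.** A moderator is a factor across whose levels the active-minus-sham difference varies. A correlation between a factor and cognitive change answers another question: whether the factor predicts change. Younger age or a lower baseline MoCA score could predict change equally under active and sham stimulation, through practice effects, regression to the mean or disease course. Such a factor would show a correlation and yet say nothing about who benefits from rTMS.

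Change in mood raises a separate problem. It is observed after treatment has begun, so treatment may shift it. Background and Rationale says of two earlier randomized trials of left-DLPFC rTMS: "Both studies reported improved depression and cognitive function". If rTMS lifts mood and better mood lifts test scores, mood change lies on the pathway from treatment to outcome. Calling it a moderator would present part of the treatment effect as a patient characteristic.

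At stake is the reading of the exploratory results. The efficacy comparison does not depend on them.

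**Working it through.** The article gives no figure for this analysis, so there is nothing to reproduce. The check has a textual part and an illustrative calculation.

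**Text: what each statement makes of mood change**

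| Place | Role given to mood |
|---|---|
| Outcomes | Change in depression, anxiety and apathy scores: secondary outcomes |
| Statistical Methods, mixed model | Anxiety and depression levels: covariates |
| Statistical Methods, moderators | Change in mood: potential moderator |
| Strengths and Limitations | Can mediate test performance; to be explored as a moderator |

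A variable that treatment may change, and that the trial itself tests as an outcome of treatment, is not a pre-treatment characteristic. Adding a mood-change-by-group interaction would not alter that.

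**Illustration: how often a Pearson test flags a factor that is not a moderator**

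Inputs from the article:
- N=66 (Objectives), taken as 33 per arm.
- 71 per group (Sample Size Determination), run as N=142 because the two sections disagree on size.
- Effect size 0.48 (Sample Size Determination).

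Assumed, not in the article:
- The factor correlates with change at r=0.3 or 0.4, equally in both arms, so true moderation is zero.
- Two-sided 5% tests.

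Approximation (Fisher z): rejection rate ≈ Φ(δ − 1.96) + Φ(−δ − 1.96), with δ = atanh(r) × √(n − 3).

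- n=33, r=0.3: δ = 0.3095 × 5.477 = 1.695, rate 0.40.
- n=33, r=0.4: δ = 0.4236 × 5.477 = 2.320, rate 0.64.
- n=66, r=0.3: δ = 0.3095 × 7.937 = 2.457, rate 0.69.
- n=66, r=0.4: δ = 0.4236 × 7.937 = 3.363, rate 0.92.
- At a weaker r=0.1 (atanh 0.1003) the rates fall to 0.085 (n=33, δ = 0.550) and 0.125 (n=66, δ = 0.796).

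Two independent simulations agree. One used 20,000 runs for the Pearson tests and 5,000 for the interaction test. The other used 4,000 runs per scenario and included the 0.48 group effect, which slightly dilutes the pooled correlation.

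| Test, zero true moderation | N=66, r=0.3 | N=66, r=0.4 | N=142, r=0.3 | N=142, r=0.4 |
|---|---|---|---|---|
| Pearson, active arm only | 0.40 | 0.65–0.66 | 0.72 | 0.94 |
| Pearson, both arms pooled | 0.67–0.70 | 0.91–0.92 | 0.95 | 0.998 |
| Regression on group and factor, no interaction | 0.69 | 0.92 | 0.96 | 0.998 |
| Factor-by-group interaction on change | 0.05 | 0.05–0.06 | 0.05 | 0.06 |

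For a pure mediator, with an assumed 0.5 SD effect of rTMS on mood, the pooled Pearson test was significant in 81% (slope 0.3) and 97% (slope 0.4) of runs at N=66.

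The Pearson rates rise with sample size because the correlation is real. The error lies in reading it as moderation, and more recruitment does not remove it.

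**Which interaction the planned model needs.** The mixed model takes baseline, end point and follow-up scores all as outcomes, so its treatment effect is group-by-time. Moderation of that effect is a factor-by-group-by-time term. A two-way factor-by-group term in that model would address group differences at baseline or averaged over time, depending on coding. On change scores, with one value per participant, the two-way term is the right one, and that is what the simulations tested.

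**The case against.** The strongest reply is that the article names regression alongside correlation. A regression with a factor-by-group term is a standard moderator analysis, and which terms enter an exploratory regression is commonly left to an analysis plan that is not shown here. This stands for the baseline-type factors. A reader might infer that prognostic factors will necessarily be reported as moderators. The text supports only that they could be, because a valid interaction model is not excluded. Age at enrollment, age at onset and disease duration are also fixed before randomization. MoCA and levodopa equivalent dose carry no stated time point, so nothing shows that post-baseline values are intended.

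The second reply is that the analysis is labelled exploratory and that Strengths and Limitations promises caution in interpreting cognitive change in the context of mood. That also stands, and it limits the severity. A reader might further infer from the abstract's conclusion about future treatment optimization that these results will be used to select responders. That conclusion refers to safety, feasibility and efficacy and does not mention moderators.

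The third reply is that the percentages rest on assumed correlations. This is correct. They are the power to detect a correlation that exists, and they count as false moderators only if a significant r alone is taken as moderation.

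Two things survive all three replies. Pearson correlation is stated as a moderator method, which it cannot be. Change in mood is listed as a moderator, which no choice of regression repairs.

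**Conclusion.** The point holds in a limited form. The article names a statistic that cannot show moderation and lists a post-randomization variable, itself a secondary outcome, as a moderator. It also uses mediator and moderator language for mood within one paragraph. These are stated choices, not detail left for later.

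For the baseline factors the risk is conditional: it arises if correlations, or regressions without an interaction, are taken as evidence. Under the assumed r of 0.3 to 0.4 at N=66, a purely prognostic factor would then be flagged in about 40% to 66% of trials (active arm) or 70% to 92% (pooled), against about 5% for the interaction test. With weaker correlations the rates are much lower. For change in mood the mislabelling does not depend on any assumed figure.

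Severity is minor. No primary or secondary comparison depends on this analysis.

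**What to change.** - Stop treating Pearson correlations as evidence of moderation. They may stay as descriptive associations if labelled so.
- Test factor-by-group-by-time terms in the planned mixed model, or factor-by-group terms on change scores, using both arms.
- Limit the factors to values measured before randomization, and say so for MoCA and levodopa equivalent dose. Use baseline depression, anxiety and apathy as the mood factors.
- Report interaction estimates with confidence intervals.
- Move change in mood to a separately labelled exploratory mediation analysis, and reword the mood sentences in Strengths and Limitations to match.

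The cost is analysis wording only. Baseline mood is already collected, and data collection is still under way, so the text can be amended before analysis. The downside is that interaction estimates will be imprecise at this sample size, and the report should say so.

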### Monitoring

#### Data Monitoring

There is no data monitoring committee for this pilot study. There is a medical monitor with whom the study team consults for safety.

#### Harms: Safety Monitoring

All study procedures and parameters are in accordance with the current safety and application guidelines for rTMS [19,21]. Treatment will be delivered by personnel trained in the administration of rTMS. An rTMS data safety monitoring sheet (DSMS), adverse event tracking log, medication log, and sleep log for each participant will be kept to monitor session attendance and any side effects or adverse events according to prespecified criteria. The Columbia-Suicide Severity Rating Scale will also be administered at the baseline, end point, and follow-up assessments.

The DSMS contains a customized severity indicator scale with before-and-after variables, including rates of change from baseline in vital signs (temperature, blood pressure, heart rate, and oxygen saturation levels), fatigue, tinnitus, sleep, dizziness, nausea, vomiting, confusion, seizure, syncope (fainting), headache, neck pain, skin integrity of the scalp, and movement. PD-related motor assessments, including speech, facial expression, finger taps, rapid alternating movement of the hands, tremor at rest, leg agility, ability to rise from a chair, gait, and body bradykinesia and hypokinesia, will also be conducted before and after each rTMS session and compared to baseline.

An adverse event tracking log will also be developed for this project for further safety monitoring. All serious and nonserious adverse events will be tracked on this log.

Sleep disruption and deprivation is associated with a lower seizure threshold, which may put the participant at a heightened seizure risk when receiving rTMS. Therefore, the sleep log asks the participants to record total hours of sleep at night and total minutes of nap time during the day. After the baseline assessment, a study team member will provide a sleep packet (collection of blank sleep logs) for the participants. The participants will then receive instructions on how to use the log. Data collected before the first rTMS session will be averaged, and variance will be documented and used as the baseline for the DSMS. At least 3 days of “total hours of sleep” will be required for the participant to complete the first session of rTMS. During the study period, self-reported sleep based on the sleep log will be checked before the intervention is administered for a given day.

Change in medication can also affect the seizure threshold. Therefore, a personalized medication log is generated for each participant. A thorough review of active medications (including prescriptions, over-the-counter medications, and supplements) will be conducted by a study team member, checked against the medical record, and reconciled with the participant to generate an accurate log of medications the participant is taking. After the baseline assessment visit, a study team member will provide a packet (collection of blank medication logs) for the participants. The participants will then receive instructions on how to use the log. During the study period, self-reported medication intake based on the medication log will be checked before the intervention is administered for a given day.

The PI has the right to terminate participation if a participant becomes uncooperative or unwilling to complete study tests, if the participant is experiencing undue stress from study procedures, or if the participant has medical problems that interfere with completion of study tests. As the long-term effects of the experimental treatment are unknown, if a participant withdraws before study completion, we recommend that they complete follow-up assessments.

### Ethical Considerations

#### Human Subject Ethics Approval

This study was approved by both the Hines VA (1337782) and Jesse Brown VA Medical Center (1395002) institutional review boards (IRBs) and is registered on ClinicalTrials.gov (NCT03836950). This study has also received an FDA investigational device exemption (G190076). Important modifications to the protocol will be communicated to the sponsor, IRB, and FDA for approval before implementation. The registration on ClinicalTrials.gov will also be updated.

#### Informed Consent

Consent will be obtained by trained study team members. All study participants will provide informed consent before completing research procedures. Participants will be given the option to opt out of consenting or research procedures at any time without loss or benefits. Research participants will have access to research staff to assist with any questions or concerns until understanding is achieved to the judgment of the individual asking the questions. A copy of the signed consent form will be provided to the participants. The consent form will indicate that data will be placed in a Hines VA IRB-approved data repository for potential future use. Only IRB-approved studies with approved data use agreements can request and use the research data for ancillary studies.

#### Privacy and Confidentiality

All hard copies of assessments will include a unique participant identification number and the date the assessment was completed. Thus, data will be deidentified. The only identifiable information will be the demographic questionnaire and contact information. The demographic questionnaire will be kept in a locked filing cabinet in the study PI’s locked office. The participants’ names and contact information will be linked to their unique study identification number and saved electronically on a secure VA crosswalk server at the Hines VA. This secure crosswalk file is the only place where the participants’ names will be linked with their unique participant identification number. The study PI will have control over the research team members who are allowed access to the crosswalk file.

#### Compensation Details

Participants will receive up to US $230 for completing all study procedures. They will receive US $25 after completing the screening visit, US $25 after completing baseline assessments, US $30 for completing the MRI scan, US $50 after the 1st rTMS session, US $50 after the 10th rTMS session, US $25 after completing end-point assessments, and US $25 after completing follow-up assessments. This compensation is intended to facilitate participation without adding undue influence.

## Results

This project was funded in June 2019, with additional funding secured in April 2024. A no-cost extension was recently received. As of April 2025, a total of 18 veterans with PD-MCI have completed the RCT phase. Data collection is ongoing and will be completed by March 2027. We expect the results of this study to be available by March 2028.

## Discussion

### Hypothesized Principal Findings

The overall research objective is to examine the therapeutic effects of rTMS on cognitive function in veterans with PD-MCI. The central hypothesis is that rTMS will safely improve cognitive function in PD-MCI. The first aim of the study is to determine the safety and feasibility of rTMS treatment. The hypothesis is that 10 high-frequency rTMS sessions will be (1) safe, as evidenced by the lack of difference in the number of research-related adverse events experienced by the active rTMS group compared to the sham rTMS group; and (2) feasible, as indicated by participant protocol completion rates. The second aim of the study is to determine the behavioral effects of rTMS. The hypothesis is that active rTMS, compared to sham rTMS, will enhance cognitive test performance after rTMS completion and at the 1-month follow-up.

### Comparison to Prior Work

Initial pilot RCTs found that multisession high frequency rTMS, targeted to the DLPFC improved depression (primary outcome) and cognitive function among patients with PD-N [14,15]. These promising results led to the design of this study protocol, which uses the 15-Hz parameter [15] but will assess cognitive function as the primary outcome among patients with PD-MCI.

Since the funding of this protocol, others have examined the effects of multisession rTMS on cognitive function (primary outcome) among patients with PD-MCI. Buard et al [16] reported no between-group differences on the total score on the Dementia Rating Scale–2 in a study that administered 20-Hz bilateral DLPFC rTMS at 90% the RMT for 10 sessions over 2 weeks. In contrast, 2 studies reported the effects of 10 sessions of high-frequency intermittent theta-burst (a patterned form of rTMS) targeted to the left DLPFC. Trung et al [17] reported improvement in visuospatial function after a 30-day follow-up in the active vs sham group. He et al [18] reported improvements in global cognitive function, immediate and delayed memory, and visuospatial ability. The improvements persisted for at least 3 months after the stimulation [18]. Finally, a meta-analysis of 14 studies suggests that multiple sessions of high-frequency rTMS over the DLPFC have positive effects on executive function in people living with PD [9]. Collectively, this evidence supports our selection of 10 sessions of high-frequency rTMS to improve cognitive function in PD-MCI.

